
### 2.11. Statistical Analyses

Descriptive statistics will be used to summarize the demographic data and baseline characteristics of each group. Data normality will be assessed using the Kolmogorov–Smirnov test. Homogeneity of variances will be evaluated using Levene’s test. Independent-samples *t*-tests and chi-square tests will be used to compare demographic characteristics between the intervention and control groups. The primary analysis will be conducted using a two-way mixed-model ANOVA to examine differences in outcome measures between groups across two assessment time points (baseline and 12 weeks). The Bonferroni correction will be used for the post hoc analysis. In case of baseline imbalances, an analysis of covariance (ANCOVA) will be conducted to compare post-intervention outcome measures between groups, with baseline scores and time since stroke included as covariates to control for potential confounding effects. However, if data are not normally distributed, appropriate nonparametric methods will be considered. The primary comparative analyses will follow the intention-to-treat principle. Missing data will be handled using multiple imputation by chained equations, generating five imputed datasets. The imputation model will include all outcome variables, baseline scores, and relevant covariates. Additionally, a per-protocol analysis will be performed for the primary outcomes to evaluate the intervention effects among participants who attended at least 80% of the sessions. Statistical significance will be set at *p* < 0.05.

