### 2.5. Sample Size

The sample size was calculated using G*Power version 3.1.9.2 based on outcome measures. Effect sizes were derived from previous studies, which reported values of 0.46 for executive function [34], 0.57 for fall risk [35], and 0.37 for gait speed [36,37]. With a power of 0.80 and an alpha level of 0.05, sample sizes of 30, 20, and 46 will be required to detect a change in executive function, fall risk, and gait speed respectively. Accordingly, a total sample size of 46 participants is considered sufficient to detect changes in outcome measures. To accommodate a 10 percent dropout rate, a total of 52 participants (26 per group) will be enrolled in the study. However, the appropriate sample size will be recalculated using data from our preliminary study.

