#### 2.8.2. Control Condition

Participants in the control group will continue their usual lifestyle or receive usual care rehabilitation during the study period, with no additional intervention. They will be encouraged to maintain their usual activities and avoid participation in other structured exercise programs outside the study intervention. The type, frequency, and intensity of concurrent treatments will be recorded and treated as covariates in the statistical analysis to control for potential confounding effects. After the 12-week period, they will be invited to participate in the intervention program according to their preference. Participants will be asked to inform the research team if there are any routine changes or unexpected events (e.g., hospital admission, illness).

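### The primary mixed ANOVA is less precise than the ANCOVA that the plan holds in reserve, and an undefined finding of baseline imbalance decides which is used

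*Protocol article*

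**What the plan says.** Section 2.11 of the protocol article sets the primary model: "The primary analysis will be conducted using a two-way mixed-model ANOVA to examine differences in outcome measures between groups across two assessment time points". The two time points are baseline and 12 weeks, so the baseline score enters as one of the two repeated measurements and not as a covariate.

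The same section gives the alternative: "In case of baseline imbalances, an analysis of covariance (ANCOVA) will be conducted to compare post-intervention outcome measures between groups". That second model would adjust for the baseline value of the outcome and for the time elapsed since the stroke. The section does not say which variables must be imbalanced, by how much, or how this is judged. The only baseline comparisons described are on demographic characteristics: t-tests, and "chi-square tests will be used to compare demographic characteristics between the intervention and control groups".

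Section 2.5 gives effect sizes of 0.46 (executive function), 0.57 (fall risk) and 0.37 (gait speed), without naming the metric, and then: "With a power of 0.80 and an alpha level of 0.05, sample sizes of 30, 20, and 46 will be required". Executive function and fall risk are the primary outcomes (section 2.10.1). Gait speed is secondary (section 2.10.2).

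**The concern.** The plan collects a baseline value of each physical and cognitive outcome and already describes the model that uses it best, but applies that model only when the observed baseline data call for it. Two things are at stake.

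- **Precision.** The default test subtracts the whole baseline score, whatever its correlation with the 12-week score. ANCOVA estimates how much of it to subtract. In a trial sized at 46 analysed participants, the difference can matter.
- **A fixed primary analysis.** Because imbalance is undefined, the primary model is settled only after the baseline data are seen. It may differ between the two primary outcomes, or be open to argument once results are known.

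**Working it through.** **1. The plan's own sample sizes.** A repeated-measures ANOVA test of the between-group factor (2 groups, 2 measurements, λ = f²·N·2/(1+ρ), with ρ = 0.5 assumed) gives N = 30 for f = 0.46, 22 for f = 0.57 (20 stated; power 0.795 at 20) and 46 for f = 0.37 (power 0.809). Then 46/0.90 = 51.1, which is 52 in two equal groups. So the stated figures are consistent with Cohen's f to within 2 participants. Read as standardised mean differences in a two-sided comparison of two means, the same values would need 150, 98 and 230. I therefore take d = 2f as the 12-week difference: 0.92 SD, 1.14 SD and 0.74 SD. This is an assumption, because the article states no metric.

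**2. Variances.** Let both visits have variance σ² and correlation r. With two visits, the group-by-time F test is the square of the t-test on change.

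- Change score: Var(Y−X) = 2(1−r)σ².
- ANCOVA: residual variance = (1−r²)σ² = (1−r)(1+r)σ².
- Ratio of ANCOVA to change score: (1+r)/2, below 1 for any r below 1.

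The change-score test therefore needs 2/(1+r) times the sample: 1.54 at r = 0.3, 1.33 at 0.5, 1.18 at 0.7 and 1.11 at 0.8. For an effect that ANCOVA detects with 80% power at N = 46, the group-by-time test needs 70, 62, 54 or 52 analysed participants.

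**3. Power at N = 46, two-sided 5%.** Noncentrality = d·√(N/4)/√v, with v = 2(1−r) or 1−r². For example, with d = 0.92 and r = 0.5: 0.92 × √11.5/√1 = 3.12 for change, and 0.92 × √11.5/√0.75 = 3.60 for ANCOVA. Each cell shows change score / ANCOVA.

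| Outcome (d) | r = 0.3 | r = 0.5 | r = 0.7 |
|---|---|---|---|
| Executive function, primary (0.92) | 0.73 / 0.89 | 0.86 / 0.94 | 0.98 / 0.99 |
| Fall risk, primary (1.14) | 0.89 / 0.98 | 0.97 / 0.99 | about 1.00 / about 1.00 |
| Gait speed, secondary (0.74) | 0.55 / 0.73 | 0.69 / 0.81 | 0.89 / 0.93 |

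**4. What the conditional switch recovers.** The trigger is undefined, so suppose it is a baseline t-test of the outcome at p < 0.05. In 100,000 simulated trials per setting (23 per arm), using the effect that ANCOVA detects with about 80% power:

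| r | Change score | Switch rule | ANCOVA always | Type I error of switch rule |
|---|---|---|---|---|
| 0.3 | 0.62 | 0.63 | 0.79 | 0.041 |
| 0.5 | 0.68 | 0.69 | 0.79 | 0.044 |
| 0.7 | 0.73 | 0.74 | 0.79 | 0.047 |
| 0.8 | 0.76 | 0.76 | 0.79 | 0.047 |

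The switch fires in about 5% of trials, so it recovers almost none of the loss.

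**5. Conditional shift.** If the arms differ by Δ at baseline, the expected 12-week difference is δ + rΔ, where δ is the treatment effect. The change score gives δ + rΔ − Δ = δ − (1−r)Δ. An unadjusted Δ of 0.5 SD shifts the estimate by 0.25 SD at r = 0.5 and by 0.15 SD at r = 0.7. Averaged over randomisations Δ is zero, and so is the shift.

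**The case against.** The strongest reply is that the default analysis is valid. Under 1:1 randomisation the change-score estimate is unbiased on average, and under the assumed trigger the type I error stays at about 4 to 5%. On the plan's own effects read as f, both primary outcomes keep more than 80% power at r of 0.5 or above. All of this stands, and it makes the point mainly one of efficiency and pre-specification.

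Four stronger readings are tempting, but the documents do not support them.

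- *A significance test chooses the model.* Section 2.11 applies its baseline tests to demographic characteristics and does not tie them to the ANCOVA. What can be said is that the trigger is undefined.
- *A loss of about 12 power points applies to the primary outcomes.* At r = 0.5 that figure (0.69 against 0.81) belongs to the gait-speed effect, which is secondary.
- *The estimate is biased.* It is shifted only conditional on an observed, unadjusted difference, and large ones are uncommon: with 26 per arm, a difference of at least 0.5 SD that a p < 0.05 test would still miss occurs in about 2.7% of trials.
- *Baseline is ignored.* The group-by-time test does use it, by subtraction.

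A reader might add that the article does not name which ANOVA effect is the treatment effect, and might question the Bonferroni step. The wording most naturally points to the interaction, the Bonferroni step is labelled post hoc, and both are details that an analysis plan can settle.

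The definition of imbalance might also sit in a plan not shown. A definition would close the open choice, but the less precise model would remain the default.

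**Conclusion.** The point holds as one that should be fixed. The primary model is less precise than the ANCOVA that the plan itself describes, for any r below 1 under randomisation with equal variances, and the choice between them is left to observed baseline data with no rule. For executive function the cost at N = 46 is about 16 power points at r = 0.3 (0.73 against 0.89), 8 at r = 0.5 and 1 at r = 0.7. For fall risk it is about 9, 2 or 3, and close to none. If the true effects are smaller than assumed, the loss is larger than these figures show, as the gait-speed row illustrates.

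These sizes rest on three assumptions: r between 0.3 and 0.8 (not given), effect sizes read as Cohen's f and applied to the 12-week difference (metric not given), and normal data with equal variances. The ordering of the two variances depends only on equal variances and randomisation.

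**What to change.** In section 2.11, for every outcome measured at baseline, pre-specify as primary the ANCOVA already described: 12-week value on randomised group, baseline value and time since stroke, whatever imbalance is seen. Report the adjusted difference with its 95% confidence interval. Delete the clause that makes ANCOVA conditional on baseline imbalance. Keep the mixed ANOVA at most as a sensitivity analysis.

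Two nearby sentences should be reconciled in the same edit. Section 2.8.2 says that concurrent treatments "will be recorded and treated as covariates in the statistical analysis to control for potential confounding effects", yet neither model in section 2.11 names them. Section 2.11 also allows an unspecified move to nonparametric methods, so the analysis could still vary by outcome unless that is fixed too.

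The cost is wording only. Baseline scores and time since stroke are already collected (sections 2.4 and 2.7), and no visit, measurement or participant is added. The change should be made before outcome data by group are seen, because the choice of model is hard to defend afterwards.

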#### 2.10.1. Primary Outcomes

Primary outcomes will be executive function and fall risk. The executive function will be measured using the Trail Making Test (TMT) [38]. This test is widely used to assess executive abilities in stroke survivors [39]. Participants will be instructed to draw lines connecting numbers in numerical order (TMT Part A) and numbers and letters in an alternating ascending sequence (TMT Part B) as quickly and accurately as possible [38]. The score for each part represents the time required to complete the task. Besides the direct scores, the B–A difference score will represent an executive function [38].

Fall risk will be assessed using the Timed Up and Go (TUG) test [40]. The TUG test has been demonstrated to be valid and to identify the risk of falling in community-dwelling older adults as well as in stroke patients [40]. Participants will be instructed to stand up from a chair, walk 3 m at their maximum safe pace, turn around, return to the chair, and sit down. Participants will be allowed to wear their usual shoes and use their assistive devices and/or orthoses if needed. The average time to complete the test in 2 trials will be recorded.

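### The analysis of the two timed primary outcomes may depend on an observed normality test, when one baseline-adjusted model per outcome could be fixed now and has more power

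*Protocol article*

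**What the plan says.** Section 2.11 sets out three linked steps.

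- **Normality check:** "Data normality will be assessed using the Kolmogorov–Smirnov test". The article does not say whether this applies per arm, pooled, per time point or to residuals, or which form of the test is meant.
- **Default analysis:** "The primary analysis will be conducted using a two-way mixed-model ANOVA to examine differences in outcome measures between groups". The two time points are baseline and 12 weeks. ANCOVA comes in only conditionally: "In case of baseline imbalances, an analysis of covariance (ANCOVA) will be conducted to compare post-intervention outcome measures between groups". Its covariates are the baseline score and the time since stroke.
- **Fallback:** "if data are not normally distributed, appropriate nonparametric methods will be considered". No method is named.

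Section 2.10.1 defines the outcomes. For the Trail Making Test, "The score for each part represents the time required to complete the task", and the B–A difference is named as the executive-function score. For the Timed Up and Go, "The average time to complete the test in 2 trials will be recorded". No transformation is mentioned. Section 2.11 also plans intention-to-treat analysis with five imputed datasets.

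**The concern.** Completion times are bounded below and usually have a long right tail, so non-normality can be planned for. Instead the article leaves the method open until a normality result is known. Three different quantities could then be reported for a primary outcome: a difference in mean change, a baseline-adjusted difference or a rank comparison. The two primary outcomes could end on different methods.

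At this sample size a Kolmogorov–Smirnov test gives an unstable answer for moderately skewed data, and the answer depends heavily on how the test is run. With five imputed datasets it could pass in some and fail in others, and the article gives no rule for that.

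At stake are a firm prespecification of the primary analysis and power that the trial could have from data it already plans to collect.

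**Working it through.** **Inputs from the article (Section 2.5).** 52 enrolled, 26 per arm; 46 needed before 10% dropout, so 46/2 = 23 per arm; 46/0.9 = 51.1, rounded up to 52 for equal arms. Effect sizes are 0.46, 0.57 and 0.37, with no metric named. Read as Cohen's f in a two-group repeated-measures ANOVA (between factors, two measurements, assumed correlation 0.5), with noncentrality N·f²·2/(1 + 0.5), they give N = 30, 22 and 46 against the stated 30, 20 and 46. On that reading 0.37 corresponds to 2 × 0.37 = 0.74 SD.

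**Assumptions not in the article.** Log-normal times with log-SD s; baseline-to-12-week correlation r on the log scale; effect in SD on the log scale. Skew is (exp(s²) + 2)·√(exp(s²) − 1). For s = 0.4 this is 3.1735 × 0.4165 = 1.32; for s = 0.6 it is 3.4333 × 0.6583 = 2.26.

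**Step 1. How often normality is rejected at the 5% level (20,000 runs, 26 per arm; r = 0.7 for the four-cell row).**

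| Implementation | Normal data | Skew 1.3 | Skew 1.75 | Skew 2.3 |
|---|---|---|---|---|
| Lilliefors, one arm | 5% | 31% | 44% | 57% |
| Lilliefors, pooled n = 52 | 5% | 55% | 74% | 86% |
| Lilliefors, any of four arm-by-time cells | 19% | 75% | 87% | 95% |
| Uncorrected fixed-parameter test, one arm | 0% | 1% | 3% | 6% |

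At the same skew of 1.3, the rate runs from 1% to 75% depending on a detail that the article does not state.

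**Step 2. What the default analysis is.** With two time points, the group-by-time interaction of the mixed ANOVA is a t-test on change scores. With equal variances at both times, the variance per patient is proportional to 2(1 − r) for change and 1 − r² for ANCOVA. The gap is 2(1 − r) − (1 − r²) = (1 − r)², which is never negative. At r = 0.5 the values are 1.00 and 0.75; at r = 0.7 they are 0.60 and 0.51.

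**Step 3. Power, 23 per arm, 0.74 SD, s from 0.3 to 0.7.**

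| Analysis | r = 0.5 | r = 0.7 |
|---|---|---|
| Change-score t-test (planned default) | 0.44 to 0.61 | 0.61 to 0.81 |
| Mann–Whitney, 12-week values | 0.65 to 0.68 | 0.65 |
| Mann–Whitney, change | 0.52 to 0.61 | 0.71 to 0.80 |
| ANCOVA, raw times | 0.68 to 0.77 | 0.82 to 0.92 |
| Rank ANCOVA | 0.77 to 0.78 | 0.88 to 0.90 |
| ANCOVA, log times | 0.79 to 0.82 | 0.92 to 0.93 |

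A hand check of the last row uses 0.74 × √(23/2) = 2.51. Divided by √0.75 this is 2.90, and divided by √0.51 it is 3.51. Set against a critical value near 2.02, these give power of about 0.80 and 0.93.

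**Step 4. A switching rule (3,000 runs, 26 per arm).** The rule uses Mann–Whitney on 12-week times if any of the four cells fails Lilliefors, and the change-score t-test otherwise. At r = 0.7 and 0.57 SD, with s = 0, 0.4 and 0.6:

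- switching rule: 0.71, 0.54, 0.50
- change-score t-test alone: 0.74, 0.62, 0.52
- Mann–Whitney on change: 0.71, 0.63, 0.60
- log-time ANCOVA (untransformed at s = 0): 0.79, 0.79, 0.80

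With no effect, the rule rejected in 4.2% to 5.6% of trials across all settings. The simulation standard error is √(0.05 × 0.95/3000) = 0.4 percentage points.

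**The case against.** Several stronger readings are tempting, and the article does not support them.

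- **That the Kolmogorov–Smirnov result decides the method.** The text says only that nonparametric methods will be considered. The link to the test is implied because it is the only normality check named.
- **That the choice is close to random.** In one arm of 26, Lilliefors rejection runs from 5% for normal data to 77% at skew 3.7, so the test does carry information. It is near a coin flip only at moderate skew.
- **That switching throws away baseline adjustment.** The default has no baseline covariate, and ANCOVA enters only under imbalance. A rank test on change or a rank ANCOVA would still use the baseline, and neither is excluded.
- **That switching costs much power.** Against the planned change-score comparison it often does not. At r = 0.5 and 23 per arm, Mann–Whitney on 12-week values does better (0.65 to 0.68 against 0.44 to 0.61). A clear loss needs the 12-week-only test together with high correlation, and at r = 0.7 also low to moderate skew. Much of the gap to log-time ANCOVA comes from adjusting for baseline at all.
- **That false positives rise.** None was seen for the rule tested. This does not cover a free choice among several methods.

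The inputs are also open to challenge. The 0.74 SD derives from gait speed, a secondary outcome. Skew and correlation are assumed, and TMT B–A was not simulated.

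A fair scope objection is that a condensed article may leave the name of the fallback test to the analysis plan. That is accepted. What remains is that the article itself makes the primary analysis conditional on observed normality, and an analysis plan that follows it would inherit that condition.

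**Conclusion.** The point holds as one of prespecification and efficiency. The method and estimand for two primary outcomes with foreseeable skew may turn on a normality result whose outcome is unstable at 26 per arm and depends on an unstated implementation. Whichever way it falls, the planned change-score comparison and the usual rank tests have less power than one baseline-adjusted model fixed in advance. For a timed outcome at 23 per arm and 0.74 SD, log-time ANCOVA exceeds the best of those alternatives by roughly 0.1 or more in power, and the planned default by up to about 0.35. It matched or beat every other analysis in all settings examined.

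These sizes rest on log-normal times and on the assumed skew, correlation and effect. For TMT B–A, the case for ANCOVA rests on the variance argument in Step 2, not on simulation. The article should be corrected before outcome data are seen, but the planned analysis is not invalid.

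**What to change.** Remove the normality test as a trigger and prespecify one model for each primary outcome:

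- **TUG:** ANCOVA on log 12-week time with log baseline time as covariate, reported as a ratio of geometric means with its confidence interval.
- **TMT:** ANCOVA on the raw B–A score with baseline B–A as covariate. A log scale does not suit B–A, which can be zero or negative. This takes B–A as the primary TMT score, which the text should confirm.
- **Checks:** residual plots as diagnostics only, with no change of primary method.
- **Sensitivity analysis:** rank-based ANCOVA, named in advance for both outcomes.

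A linear-model estimate with a standard error can also be combined across the five imputed datasets in the usual way, which a Mann–Whitney p-value cannot.

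The cost is a change of wording. No extra data or patients are needed. The downside is that the TUG effect is reported as a percentage difference and not in seconds.

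### Five imputed datasets leave avoidable random noise in borderline primary p-values; a larger number would remove most of it at almost no cost

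*Protocol article*

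**What the plan says.** Section 2.11 (Statistical Analyses) states: "The primary comparative analyses will follow the intention-to-treat principle". It goes on to say that missing values are to be imputed by chained equations, "generating five imputed datasets". On the content of the imputation model it says: "The imputation model will include all outcome variables, baseline scores, and relevant covariates". The analysis that these datasets feed is a group-by-time ANOVA with two time points, baseline and 12 weeks, and the significance level is p < 0.05.

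Section 2.5 (Sample Size) gives the expected amount of missing data: "To accommodate a 10 percent dropout rate", the target of 46 is raised to 52. Section 2.10.1 names two primary outcomes, executive function (TMT) and fall risk (TUG). Table 1 schedules both only at baseline and week 12.

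The article gives no reason for five, no rule linking the number of imputations to the amount of missing data, and no check of Monte Carlo error.

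**The concern.** Multiple imputation is a random procedure. The pooled estimate, its standard error and its p-value all vary from run to run, and the variation shrinks as the number of imputed datasets, m, grows. With m = 5 the point estimate is already nearly as precise as it can be, but the p-value is less stable than that suggests.

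This matters because the trial reads each primary result against a fixed threshold. If the result lies close to 0.05, two analysts who follow the same plan on the same data could report opposite conclusions. The imputations will be needed: a participant who drops out has no post-treatment value for either primary outcome, because week 12 is the only post-baseline assessment of both. What is at stake is the reproducibility of a borderline finding.

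**Working it through.** **Inputs from the protocol article**
- m = 5 and the threshold p < 0.05: section 2.11.
- Dropout 10%, N = 52: section 2.5. The article's own figure reproduces: 46 / (1 − 0.10) = 51.1, rounded up to 52 for two equal groups. Expected dropouts: 0.10 × 52 = 5.2, so about five people.

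**Input assumed**
- Fraction of missing information (FMI) for the treatment effect. The article does not give it. It is set to 0.10, equal to the planned dropout, with 0.20 as the upper end of the range.

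**Step 1. Noise in the test statistic.** Approximately, the Monte Carlo SD of z is √(FMI / m).
- FMI 0.10, m = 5: √0.020 = 0.141
- FMI 0.10, m = 50: √0.002 = 0.045
- FMI 0.20, m = 5: √0.040 = 0.200

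**Step 2. Effect on a borderline p-value.** Take z = 2.0, two-sided p = 0.046, and move it by plus or minus 1 SD.

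| FMI | m | z range | p range |
|---|---|---|---|
| 0.10 | 5 | 1.859 to 2.141 | 0.032 to 0.063 |
| 0.10 | 50 | 1.955 to 2.045 | 0.041 to 0.051 |
| 0.20 | 5 | 1.800 to 2.200 | 0.028 to 0.072 |

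**Step 3. How often this would matter.** Step 2 is conditional on a borderline result. For the unconditional chance, let the result with unlimited imputations be z∞ ~ N(δ, 1), where δ is set by the true power. Let the result with m imputations be z∞ plus N(0, FMI / m) noise. The quantity wanted is the probability that the two fall on opposite sides of the two-sided 0.05 threshold, for one primary test.

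| FMI | Scenario | m = 5 | m = 50 |
|---|---|---|---|
| 0.10 | No effect | 1.3% | 0.4% |
| 0.10 | 80% power | 3.1% | 1.0% |
| 0.10 | 90% power | 2.0% | 0.6% |
| 0.20 | 80% power | 4.5% | 1.4% |

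These are small because p-values near 0.05 are uncommon. Under the same model, p lies between 0.03 and 0.07 in about 10% of trials at 80% power and in 4% under no effect.

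**Step 4. Check by simulation.** The formula ignores noise in the estimated between-imputation variance and in the degrees of freedom. A simulation that includes both used N = 52, 10% of week-12 values missing completely at random, an assumed baseline-to-week-12 correlation of 0.5, imputation from baseline and group, and Rubin's rules with small-sample degrees of freedom. FMI came out at about 0.08. For data whose stable p-value (at 20,000 imputations) is known:

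| Stable p | m | Runs on the other side of 0.05 |
|---|---|---|
| 0.04 | 5 | 29% |
| 0.04 | 20 | 10% |
| 0.04 | 50 | 2% |
| 0.06 | 5 | 25% |
| 0.06 | 20 | 10% |
| 0.06 | 50 | 2.5% |

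At m = 5, a stable p of 0.03 or 0.07 still crosses in 10% to 11% of runs. So the conditional noise is somewhat larger than the simple formula suggests, and the m = 5 figures in step 3 may be a little low.

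**The case against.** The strongest case for leaving the plan alone is that five imputations is a valid, prespecified choice. Rubin's rules carry the finite number of imputations in the variance and the degrees of freedom, so tests and intervals remain honest. The efficiency cost is small: relative efficiency is 1 / (1 + 0.10 / 5) = 0.98. All of this stands. Efficiency, however, describes the estimate and not the repeatability of the p-value on which the result is judged.

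Three stronger readings are tempting, and the documents do not support them.
- *The primary analysis is biased or unreliable.* It is not. The noise is centred on the right answer, and a clear result stays clear. The 25% to 29% in step 4 applies only to data already close to 0.05; over all possible results the figure is 1.3% to 4.5%.
- *The missing seed is a defect that lets the analyst choose the result.* A seed is commonly left to the statistical analysis plan or the code, neither of which is shown. Nor can its timing be tied to unblinding, because section 2.6 blinds only the assessors and describes no unblinding step.
- *Fifty is a required minimum.* The article sets no tolerance from which a minimum could be derived. Twenty already removes much of the noise, and no finite number settles a p-value of exactly 0.05.

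It can also be said that the planned imputation model, with all outcomes and covariates, would lower the missing information. That is possible where only some measurements are missing. A participant who misses week 12 altogether lacks the other week-12 outcomes too, so the gain there is limited.

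**Conclusion.** The point holds as a minor, nearly free improvement. Five imputed datasets give a borderline primary p-value a visible random component that 50 would largely remove: at z = 2.0, 0.032 to 0.063 against 0.041 to 0.051. Per primary test, the overall chance of crossing 0.05 through imputation noise is about 1.3% to 4.5% with five and 0.4% to 1.4% with 50.

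These figures rest on missing information of 0.10 to 0.20, which the article does not state, and on a normal approximation. The simulation adds data missing completely at random, a correlation of 0.5 and a simplified imputation model. More missing data would widen the ranges and strong auxiliary variables would narrow them. The issue is reproducibility, not validity, and the article states nothing false here.

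**What to change.** In section 2.11, replace five with a larger number of imputed datasets, for example 50 or more. The cost is one number in the text and seconds of computing. Recording the seed before the analysis is run is good practice and belongs in the statistical analysis plan or the code. It does not replace the larger number: a fixed seed with five datasets makes the result repeatable but still dependent on an arbitrary draw.
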